## Abstract

**Background:**

Sickle cell disease (SCD) is a genetic disorder which causes dysfunctional red blood cells (RBC) and is thought to increase requirements for folate, an essential B vitamin, due to increased RBC production and turnover in the disease. High-dose supplementation with 1–5 mg/d folic acid, synthetic folate, has been the standard recommendation for children with SCD. There is concern about whether children with SCD need such high doses of folic acid, following mandatory folic acid fortification of enriched grains in Canada, and advancements in medical therapies which extend the average lifespan of RBCs. In animal and human studies, high folic acid intakes (1 mg/d) have been associated with accelerated growth of some cancers, and the biological effects of circulating unmetabolized folic acid (UMFA), which can occur with doses of folic acid ≥ 0.2 mg/d, are not fully understood. The objective of this study is to determine efficacy of, and alterations in folate metabolism from high-dose folic acid in children with SCD during periods of folic acid supplementation versus no supplementation.

**Methods:**

In this double-blind randomized controlled cross-over trial, children with SCD (*n* = 36, aged 2–19 years) will be randomized to either receive 1 mg/d folic acid, the current standard of care, or a placebo for 12 weeks. After a 12-week washout period, treatments will be reversed. Total folate concentrations (serum and RBC), different folate forms (including UMFA), folate-related metabolites, and clinical outcomes will be measured at baseline and after treatment periods. The sum of the values measured in the two periods will be calculated for each subject and compared across the two sequence groups by means of a test for independent samples for the primary (RBC folate concentrations) and secondary (UMFA) outcomes. Dietary intake will be measured at the beginning of each study period.

**Discussion:**

As the first rigorously designed clinical trial in children with SCD, this trial will inform and assess current clinical practice, with the ultimate goal of improving nutritional status of children with SCD.

**Trial registration:**

ClinicalTrials.govNCT04011345. Registered on July 8, 2019

## Administrative information

Note: the numbers in curly brackets in this protocol refer to SPIRIT checklist item numbers. The order of the items has been modified to group similar items (see http://www.equator-network.org/reporting-guidelines/spirit-2013-statement-defining-standard-protocol-items-for-clinical-trials/).

## Introduction

### Background and rationale {6a}

Sickle cell disease (SCD) is a rare, inherited hemoglobinopathy that affects over 5000 Canadians, including 3000 children and youth [1]. In SCD, variants in the β-globin gene produce an abnormal sickle-hemoglobin molecule (HbS), which forms a rigid sickle shape upon release of oxygen due to polymerization [2, 3]. While the severity of disease can vary among homozygous and heterozygous genotypes, hallmarks of the disease include hemolytic anemia, vaso-occlusion, stroke, ischemic tissue damage, organ failure, and severe pain in the back, extremities, thorax, abdomen, and central nervous system [4–6]. Chronic hemolytic anemia and increased red blood cell (RBC) production and turnover in SCD are thought to increase the requirements of folate, a water-soluble family of compounds that are essential for erythropoiesis [7, 8]. Naturally occurring folate is commonly found in foods such as leafy green vegetables, oranges, beans, and legumes [9], while dietary supplements and folate-fortified foods commonly contain folic acid (FA), the synthetic oxidized version of folate, due to its stability and higher bioavailability [10].

The Canadian Haemoglobinopathy Association recommends supplementation of 1–5 mg per day (mg/d) of FA in individuals with SCD in Canada [1], largely based on studies conducted between 1975 to 2001 that showed individuals with SCD had low blood serum or RBC folate concentrations [11–13]. The lowest recommended dose of 1 mg/d FA, however, provides 6 times more folate than is recommended for healthy children aged 1–3 years [14].

The biological effects of FA are not fully understood. In order to be biologically active, FA is reduced to dihydrofolate by dihydrofolate reductase (DHFR). However, the capacity for DHFR to metabolize large amounts of FA may be limited [15]. Recent studies suggest that the maximal capacity for this process is much lower than was previously thought, so even intakes of FA as low as 0.2 mg will leave an appreciable amount of unmetabolized folic acid (UMFA) to be taken up into circulation [15, 16].

There is limited evidence that FA supplementation improves hematological or clinical outcomes in individuals with SCD [7]. Effectiveness of FA supplementation was largely investigated in the 1970–1980s and presented inconclusive evidence [13, 17–20]. A 1983 trial among 117 Jamaican children with SCD aged 6 months to 4 years, the only trial eligible for inclusion in the Cochrane Review of FA supplementation in individuals with SCD, examined the effect of 5 mg/d FA versus a placebo [21]. Although authors observed an increase in serum folate levels (concentrations below 11 nmol/L were evident in 15% (*n* = 6/39) of children in the placebo group versus none of the folic acid group, while concentrations above 40 nmol/L were evident in 81% (*n* = 33/41) of the folic acid group versus 15% in the placebo (*n* = 15/39) group) after 1 year in those treated with FA, no effect on hemoglobin, growth parameters, or other clinical events was observed [21]. The quality of the evidence, however, was low due to the high risk of bias in random sequence generation and incomplete data, making it difficult to draw conclusions from this trial [7].

There is mounting concern about whether Canadian children with SCD require high doses of FA, especially given the mandatory FA fortification of refined grains, specifically white flour, enriched pasta, and enriched corn meal, in Canada since 1998. It is estimated that Canadian children consume, on average, 331 ± 123 μg (*n* = 2193; children aged 1–3 years) to 699 ± 225 μg (*n* = 2397; adolescent males aged 14–18 years) per day of dietary folate equivalents (from both naturally occurring folate and folic acid) [22]. With intake levels of this magnitude, the majority of Canadian children are predicted to meet the recommended dietary allowance for folate from food sources alone. Furthermore, the Canadian Health Measures Survey in 2011 showed that less than 1% of Canadians (*n* = 5248, 6–79 years) had folate deficiency (RBC folate < 305 nmol/L) and 40% had high RBC folate concentrations (> 1360 nmol/L) [23]. In Canadian children with SCD, a recent Canadian study (*n* = 87, age 2–17 years) reported that there was no evidence of serum folate deficiency among individuals supplemented with 1 mg/d FA [24].

Advancements in medical therapy, specifically the use of hydroxyurea, a medication which extends the average lifespan of RBCs from a mean of 4.1 ± 2.71 days to 21.3 ± 6.44 days through the promotion of fetal hemoglobin concentrations [25, 26], may also decrease folate requirements because of reduced RBC turnover. A 2017 study of US children with SCD (*n* = 72), the majority (96%) of which were prescribed hydroxyurea, reported that discontinuation of 1 mg/d FA for ~ 80 days did not change RBC folate concentrations and mean RBC folate concentrations remained high (4 times higher than the suggested World Health Organization deficiency cutoff of 340 nmol/L [16]) after the discontinuation [27].

There is growing concern that higher FA intakes may lead to adverse health outcomes, as intakes of 1 mg/d FA have been associated with acceleration of mammary tumors in rats [28], and colorectal [29] and prostate [30] cancer in adults. There is also evidence that excess FA intakes may have adverse effects on metabolic health during development [31, 32] suggesting young children undergoing periods of rapid growth and development are especially vulnerable. The association of adverse health outcomes with high FA intake remains controversial, but debate has limited some countries from adopting mandatory nationwide FA fortification programs due to these concerns [33].

As no well-designed randomized controlled trial of FA supplementation on children with SCD has been conducted to date, the aim of this study is to determine if high-dose FA supplementation is efficacious, safe, and warranted in children with SCD.

### Objectives {7}

The primary objective is to assess the efficacy of high-dose FA supplementation by measuring the effect of 12 weeks of 1 mg/d FA on RBC folate concentrations, serum folate concentrations, and clinical outcomes (occurrence of megaloblastic anemia and acute pain crises) in children with SCD, compared to placebo.

The secondary objective is to assess alterations in folate metabolism from high-dose FA supplementation by measuring the effect of 12 weeks of 1 mg/d FA on plasma UMFA concentrations, and folate-related metabolite concentrations (plasma *S*-adenosylmethionine, *S*-adenosylhomocysteine, total homocysteine, vitamin B_12_, and methylmalonic acid) in children with SCD, compared to placebo.

We hypothesize that (1) none of the children will present with folate deficiency (RBC folate < 340 nmol/L) during the study period, (2) mean RBC folate concentrations will be similar following 12 weeks of FA or placebo supplementation, showing no benefit of FA supplementation, and (3) plasma UMFA concentrations will be higher following 12 weeks of FA supplementation compared to levels following the placebo supplementation.

### Trial design {8}

This is a double-blind randomized controlled cross-over trial consisting of a 12 ± 1-week intervention period (treatment of 1 mg/d FA or placebo), followed by a 12 ± 1-week wash-out period and a reversal of treatments. The 12-week duration of the intervention and washout periods is based on the estimation that steady-state conditions of RBCs in children with SCD receiving hydroxyurea is reached before 80 days [27]. Approximately 60% of the children with SCD at BC Children’s Hospital are prescribed hydroxyurea [34]. The 12-week washout period will minimize the risk of any carryover effect of the first treatment.

The distinguishing advantage of a cross-over trial from a conventional parallel-arm trial is that each child will serve as his/her own control, thus reducing the bias of confounding variables (e.g., age, sex, dietary intake) [35]. This design will also allow us higher power (lower sample size requirement) to determine a statistically significant treatment effect [35].

A non-inferiority framework will be used to determine whether placebo is inferior or non-inferior to FA, the current standard, for the maintenance of red blood cell folate concentrations.

## Methods: participants, interventions, and outcomes

### Study setting {9}

This trial will occur at BC Children’s Hospital (Canada), an affiliate academic hospital of the University of British Columbia (Canada).

### Eligibility criteria {10}

Individuals will be eligible for participation if (1) they have a confirmed diagnosis of SCD, (2) they are aged 2–19 years and attend BC Children’s Hospital for medical care, and (3) they have received routine daily supplementation of FA for the prior 12 weeks.

Individuals will be excluded from participation if (1) they have received a blood transfusion in the previous 12 weeks, (2) they are allergic to any components of the supplements (cellulose, methylcellulose, magnesium stearate, and/or titanium dioxide), (3) they have presented with megaloblastic anemia in the previous 12 weeks, (4) they have current pulmonary, renal, and/or cardiac complications (severe or recurrent acute chest syndrome), (5) they routinely take medications known to interfere with B vitamin metabolism (chloramphenicol, methotrexate, metformin, sulfasalazine, phenobarbital, primidone, triamterene, barbiturates), (6) they are currently pregnant, planning to become pregnant in the next 9 months, or currently breastfeeding, (7) they have participated in a clinical research trial in the previous 30 days, (8) they have donated blood in the previous 30 days, or (9) they have an unstable medical condition or laboratory results.

### Who will take informed consent? {26a}

Eligible individuals and their parents/legal guardians will be approached by the study coordinator ([name]) with information regarding the study at the out-patient hematology clinic at BC Children’s Hospital. Written informed consent and child or adolescent assent, as applicable, will be obtained.

### Additional consent provisions for collection and use of participant data and biological specimens {26b}

Not applicable

### Interventions

#### Explanation for the choice of comparators {6b}

In this trial design, each participant will receive the current standard of care, 1 mg/d FA, and a placebo comparator for 12 ± 1 weeks. As previous studies have illustrated children with SCD prescribed routine prophylactic FA (1 mg/d) continue to have mean red blood cell folate concentrations 4 times higher than deficiency cutoffs after discontinuation of FA supplementation [27], a placebo comparator was chosen given that treatment (supplementation) may be unnecessary in children, and folate concentrations are speculated to be adequate regardless of treatment group.

#### Intervention description {11a}

Supplements are packaged in bottles containing 100 opaque capsules. The tablets, bottles, and labels on the bottle are identical in appearance except for a sticker which identifies the treatment group (A or B). Supplements will be dispensed from the BC Children’s Hospital Pharmacy at the beginning of each intervention period. Supplements will contain 1 mg FA or placebo, to be taken daily in the morning with food, for the 12 ± 1-week intervention periods. Individuals who cannot swallow capsules may open the capsules and add the powdered supplement to food products.

Supplements were manufactured by Natural Factors Nutritional Products Ltd. (Coquitlam, British Columbia, Canada), and a Notice of Authorization for the purposes of this clinical trial was obtained from the Natural and Non-Prescription Health Products Directorate of Health Canada on December 4, 2019.

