### Participant timeline {13

#### Sample size {14}

Sample size was estimated using data from the recent Nguyen et al. [27] study in the USA to estimate means and standard deviation for RBC folate from children with SCD who had 1 mg/d FA discontinued. This population is similar to our clinical population in terms of national FA fortification policies and clinical management. A non-inferiority approach was used to determine the sample size needed to assess the efficacy of 1 mg/d FA as compared to the placebo. Assuming a single group standard deviation in RBC folate of 150 ng/mL (340 nmol/L) observed post-FA discontinuation, a difference in means between groups of 30 ng/mL (68 nmol/L) [27], power of 0.8, alpha of 0.05, and a non-inferiority margin of 100 ng/mL (227 nmol/L) determined based on clinical significance, 28 children (14 in each treatment order) are needed to confirm that the RBC folate concentrations are at most 100 ng/mL (227 nmol/L) lower during the placebo period than during the FA supplementation period.

Sample size was rounded up to 36 children (18 in each treatment order) to account for attrition and to be powered to detect clinically meaningful differences in our secondary outcome (UMFA concentrations).

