### Assignment of interventions: allocation

#### Sequence generation {16a}

An independent research assistant from Natural Factors Nutritional Products Ltd. (Coquitlam, British Columbia, Canada) assigned blinding codes (A or B) to the FA and placebo supplements. The allocation sequence to treatment A or B was determined by a statistician unassociated with the study, under the direction of a clinical trialist (JS), via computer-generated random numbers in SAS statistical software, stratified in blocks of four to ensure roughly equal distribution of treatment order allocations during the study duration.

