### Assignment of interventions: blinding

#### Who will be blinded {17a}

Clinicians/care providers, study personnel, outcome assessors, data analysts, and participants will be blinded to the allocation sequence. The sequence allocation will be kept confidential by research pharmacy personnel until full data analysis has been completed.

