#### Procedure for unblinding if needed {17b}

In an emergency situation, in which the health and safety of a participant is at risk, breaking the code of the double-blinded study may be done at the request of a medical practitioner responsible for the medical management of a participant to (1) to reveal treatment assignment to inform further medical treatment, (2) to provide information about the nature and risks of the particular treatment the participant is or has received, or (3) for the Principal Investigator to advise about the nature and risks associated with a particular treatment. The research pharmacy may make the randomization assignment result available to the Principal Investigator ([name]), for communication to the requesting clinician, upon reasonable request.

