### Oversight and monitoring

#### Composition of the coordinating center and trial steering committee {5d}

A multi-disciplinary steering committee was established to guide the research trial from conception to completion. Membership includes the Primary Investigator ([name]), the SCD Clinic Hematologist ([name]), and the SCD Nurse Clinician (HM). The steering committee will also lead knowledge translation planning activities. The data management team will consist of the study coordinator ([name]) and Principal Investigator ([name]).

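### Two product-level codes (A or B) mark all supplies, so one emergency code-break gives the key to both letters and weakens blinding beyond the child concerned

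*Protocol article*

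**What the plan says.** All references are to the protocol article.

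- **Labelling.** Intervention description {11a} says the supplies are "identical in appearance except for a sticker which identifies the treatment group (A or B". The article mentions no bottle-level or child-level code.
- **What the letters mean.** Under Sequence generation {16a}, an assistant at the manufacturer "assigned blinding codes (A or B) to the FA and placebo supplements". The same section adds: "The allocation sequence to treatment A or B was determined by a statistician unassociated with the study".
- **Design.** Trial design {8} describes one intervention period, "followed by a 12 ± 1-week wash-out period and a reversal of treatments". Sample size {14} sets 36 children, 18 in each order.
- **Blinding promise.** Who will be blinded {17a} covers care providers, study personnel, outcome assessors, analysts and participants, and adds: "The sequence allocation will be kept confidential by research pharmacy personnel until full data analysis has been completed".
- **Code-break.** Procedure for unblinding {17b} permits a break in an emergency at the request of the responsible practitioner. On the route it says: "The research pharmacy may make the randomization assignment result available to the Principal Investigator". The principal investigator then informs the clinician.
- **Other role of the recipient.** Section {5d} says: "The data management team will consist of the study coordinator" and the principal investigator. The principal investigator also sits on the steering committee.

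**The concern.** A code-break should cost the trial the blinding of one child. When the only codes are two letters fixed to the two products, the answer to one request also says what the letter means on every other bottle. The person through whom that answer passes has data-management and oversight roles for the rest of the trial.

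What is at stake is the blinding promised in {17a} for the children who had no emergency. The exposed parts are those that involve report or judgement. Acute pain crises are self-reported and are named in the primary objective, although the Outcomes section classes them as a secondary clinical outcome. Premature withdrawal can follow poor compliance or serious adverse events, which leaves room for discretion.

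**Working it through.** The article gives no expected number of code-breaks, so there is no figure of the plan to reproduce. The check is a reading of the sections side by side, plus counting.

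**Step 1: do the letters denote a product or a sequence?** The phrase about treatment group in {11a} could, taken alone, mean a sequence group. Section {16a} settles it, because the codes were given to the FA and placebo supplements. One letter is FA and the other is placebo, for every child and in both periods.

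**Step 2: what does one break reveal?** A break under {17b} gives the actual product for one child. Anyone who also knows the letter on that child's bottle has one pair (letter, product). With only two letters and two products, the second pair follows by elimination.

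**Step 3: how far does the key reach?**
- Children: 36. Periods per child: 2. Child-periods under the same two letters: 36 × 2 = 72.
- Because treatments are reversed, a child's letter in either period gives that child's whole sequence.
- With participant- and period-specific codes, the same break would expose 1 child of 36, that is 2 child-periods of 72.

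**Step 4: what else is needed to decode another child?** Two facts are required: the meaning of the letters and the letter of that child.
- After a break, the route in {17b} can give the principal investigator the first fact.
- The second is on a bottle that the family holds for about 12 weeks.
- The article does not say that the principal investigator or the coordinator sees the letters. The pharmacy dispenses, and the lead research pharmacist assigns the order and counts capsules.

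The 72 child-periods are therefore the reach of the key, an upper limit and not a count of children who would be unblinded.

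**Step 5: which outcomes are exposed?** RBC folate (primary) and plasma UMFA are measured by LC-MS, so knowledge of the allocation has little scope to alter them. Capsule counts are made by the pharmacist, who already holds the sequence and the codes ({16b}), so a break changes nothing there. Self-reported pain crises, and decisions such as withdrawal, remain.

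**The case against.** A reader might infer that a single break unblinds the whole trial. The documents do not support that. Families can see a letter but are not told its meaning. The principal investigator may learn the meaning but is not shown to receive the letters of the other children. Telling the principal investigator and one clinician also does not in itself unblind the other 35 families who report pain crises. This objection stands and limits the point to children whose letter is known and to any data labelled A/B.

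A reader might also see a contradiction between {17a} and {17b}. There is none: {17b} is the ordinary emergency exception and is worded for one participant. The weakness is that two-letter labelling prevents the exception from being confined to that participant.

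Nor do the documents support a probability of harm. They give no code-break rate. Acute events in this disease are not code-breaks, since {17b} requires an emergency and a practitioner's request.

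Finally, a pharmacy manual or the full protocol might add a participant label or cover the sticker. The article does not say so. What it does state is that the sticker with the letter is the visible difference between the bottles, and the point rests on that statement.

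**Conclusion.** The point holds as a structural weakness of moderate size. Two product-level codes, shown on the bottle, serve 36 children and 72 child-periods. One break reveals what both letters mean, along a route that includes a member of the data management team. The blinding promised in {17a} is then weaker than it need be for every child whose letter is known.

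The conclusion rests on three conditions: a break occurs; the person who receives the answer can pair it with a letter; and that person knows, or comes to know, other children's letters. The article establishes none of these as events. It establishes only that the labelling offers no protection if they happen. The effect on RBC folate and UMFA is small. The effect on self-reported pain crises and on judgement-based decisions could matter, but cannot be quantified from the documents.

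**What to change.** Have the research pharmacy cover the A/B sticker at dispensing with a participant- and period-specific number, taken from a list that only the pharmacy holds. State this in {11a}, and note in {16a} that the letters are for supply and pharmacy use only. A code-break then discloses the assignment of that child and no other. The emergency access in {17b} can stay as written, including the principal investigator's role in advising on the treatment.

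Recruitment began in February 2020, so some bottles may already be in use with the letter showing. The change can still be applied to every bottle not yet dispensed, including second-period bottles for children already enrolled.

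The cost is about 72 labels and a code list to maintain. At 100 capsules per bottle and at most 13 × 7 = 91 days per period, one bottle covers a period, so 36 × 2 = 72 bottles. The pharmacy already dispenses each bottle and holds the sequence and the codes, so no new product or assay is needed.
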